**Figure 1 f1:**
[figure not shown]
Study design of the randomized controlled trial.

In this scenario, the 2:1 ratio was chosen for the following reasons: i) the study devices are deemed to be safe and able to provide timely monitoring of participants health status, thus 1) possibly improving their condition as compared to the control group and 2) minimizing the number of patients not exposed to this potential benefit; ii) the platform acts unobtrusively, and it favors contact with healthcare professional which is normally very well accepted and pursued by patients; moreover it is designed to allow for patients’ empowerment; iii) we anticipate that costs associated with SoC not supported with the BD4QoL platform will be superior because subjects randomized in the intervention arm are deemed to experience less adverse events than controls. In this context, a cost-effectiveness analysis is planned as an exploratory endpoint (**Table 2**).

As stated by Palmer et al., favoring the experimental therapy is warranted in trials of potentially significant public health benefit (21). Unequal allocation schemes can improve recruitment and partially satisfy the individual ethics criterion (the study participants have a higher probability of being randomized in the intervention arm than in control one). They can also be useful if widespread knowledge about the control therapy already exists and if more understanding is desired about the new treatment.

The randomization procedure will be web-based, centralized, computerized (software-generated randomization list using RedCap web-based platform) (22, 23). Local research teams will be blinded to the randomization list (local people designated to the randomization procedure will not know the randomization list, but clinical investigators will not be blinded to the outcome of the randomization). The biostatistician doing the analysis of the trial will be blinded to the list as well until the statistical analysis plan, previously defined, is signed.

The EORTC QLQ-C30 (4), EORTC QLQ-HN43 (6), EQ-5D-5L (8), and CBI-B (11) evaluations will be performed at 0-, 6-, 12-, 18-, 24-month from randomization. The time zero is considered to be the date of randomization. The scores of the EORTC QLQ instruments [as defined in (13, 14)] will be compared to the respective scores of the previous study time-point.

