## Abstract

Patients surviving head and neck cancer (HNC) suffer from high physical, psychological, and socioeconomic burdens. Achieving cancer-free survival with an optimal quality of life (QoL) is the primary goal for HNC patient management. So, maintaining lifelong surveillance is critical. An ambitious goal would be to carry this out through the advanced analysis of environmental, emotional, and behavioral data unobtrusively collected from mobile devices. The aim of this clinical trial is to reduce, with non-invasive tools (i.e., patients’ mobile devices), the proportion of HNC survivors (i.e., having completed their curative treatment from 3 months to 10 years) experiencing a clinically relevant reduction in QoL during follow-up. The Big Data for Quality of Life (BD4QoL) study is an international, multicenter, randomized (2:1), open-label trial. The primary endpoint is a clinically relevant global health-related EORTC QLQ-C30 QoL deterioration (decrease ≥10 points) at any point during 24 months post-treatment follow-up. The target sample size is 420 patients. Patients will be randomized to be followed up using the BD4QoL platform or per standard clinical practice. The BD4QoL platform includes a set of services to allow patients monitoring and empowerment through two main tools: a mobile application installed on participants’ smartphones, that includes a chatbot for e-coaching, and the Point of Care dashboard, to let the investigators manage patients data. In both arms, participants will be asked to complete QoL questionnaires at study entry and once every 6 months, and will undergo post-treatment follow up as per clinical practice. Patients randomized to the intervention arm (n=280) will receive access to the BD4QoL platform, those in the control arm (n=140) will not. Eligibility criteria include completing curative treatments for non-metastatic HNC and the use of an Android-based smartphone. Patients undergoing active treatments or with synchronous cancers are excluded.

Clinical Trial Registration: ClinicalTrials.gov, identifier (NCT05315570).

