### Study objectives and endpoints

2.1

The overall aim of this study is to assess if QoL deterioration can be anticipated and prevented by the addition of the BD4QoL platform to standard of care (SoC) versus SoC alone, in HNC survivors post-treatment with up to 24-month follow-up. Primary and secondary objectives and endpoints are specified in **Table 1**, exploratory ones in **Table 2**.

**Table 1 T1:** Study objectives and endpoints.

	Objective	Endpoint
** *Primary* **	To reduce the proportion of HNC subjects experiencing a clinically meaningful deterioration of QoL between at least 2 visits during post-treatment follow-up.	The proportion of HNC survivors experiencing a clinically relevant deterioration in the global health scale of the EORTC QLQ-C30 [decrease ≥10 points, as defined in (13,14)] within the study observation (up to 24 months) period during post-treatment follow-up.
** *Secondary* **	To delay the time to the first clinically meaningful deterioration of QoL between at least 2 visits during post-treatment follow-up.	The time to first clinically relevant deterioration of EORTC QLQ-C30 global score [decrease ≥10 points, as defined in(13,14)] measured within the study observation (up to 24 months) period during post-treatment follow-up.
	To reduce the proportion of HNC subjects experiencing a clinically relevant deterioration in pre-specified QoL domains between at least 2 visits during post-treatment follow-up.	The proportion of HNC survivors experiencing a clinically meaningful deterioration [as defined in (13,14)] of pre-specified EORTC QLQ-C30 scales (emotional functioning, role functioning, sleep) within the study observation (up to 24 months) period during post-treatment follow-up.
	To reduce the proportion of HNC subjects experiencing a clinically meaningful deterioration in pre-specified head and neck cancer specific QoL domains between at least 2 visits during post-treatment follow-up.	The proportion of HNC survivors experiencing a clinically relevant deterioration of pre-specified EORTC QLQ-HN43 scales (swallowing, problems with teeth, problems opening mouth, speech, social eating, fear of progression, emotional functioning, fatigue) within the study observation (up to 24 months) period during post-treatment follow-up.

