### Study design

2.2

This is a multicenter, international, two-arm, randomized (2:1 ratio), open-label, superiority trial, designed to evaluate the proportion of HNC survivors experiencing a clinically meaningful QoL deterioration [reduction of at least 10 points in EORTC QLQ-C30 global health status (13, 14)] between at least 2 visits during post-treatment follow-up (up to 24 months from randomization) with the use of the BD4QoL platform through the web-forms tool for QoL questionnaires answers and through continuous monitoring by a mobile application (App) installed on the study subject’s mobile phone in comparison to those without the BD4QoL platform (SoC). If a clinically relevant deterioration in global health, measured with the EORTC QLQ-C30 global health scale [decrease ≥10 points, as defined in (13, 14)] is detected during the study period, the subject participation in the study will be interrupted (because the aforementioned decrease would imply that the primary endpoint is not met for a specific participant).

Patients will be followed up as per clinical practice (18, 19):

a. All subjects will be asked to complete validated questionnaires [EORTC QLQ-C30 (4), QLQ-HN43 (6), and EQ-5D-5L (7), CBI-B (11)] and PREM on up to 5 occasions over a 2-year period, at randomization (0-month of follow-up), then once every 6 months ± 2 months (after 6, 12, 18, 24 months from randomization).

b. Participants in both arms will be offered routine SoC and asked to complete validated QoL questionnaires at regular intervals (described above). In addition, those in the intervention arm will be offered the device-generated data collection platform (BD4QoL device *plus* QoL validated questionnaires *plus* counseling and physician contact triggered by the data generated by the platform [early intervention] *plus* a possible psychological effect of the whole activities in the interventional arm). A 2:1 randomization will be used (2/3 of subjects with BD4QoL platform versus 1/3 of subjects without). Participants randomized to the control arm will not receive the above-mentioned platform; they will fill in the same validated questionnaires on web-based instruments and will be followed up as per usual clinical practice.

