#### Sample size

2.5.1

The primary endpoint is the proportion of HNC survivors experiencing a clinically relevant deterioration in global health-related QoL as previously defined.

In the European BD2Decide project (31), funded by the Horizon 2020 program and concluded in November 2019, the analysis of QoL questionnaires was performed on over 450 stage III-IV HNSCC patients (recruited from Italy, Germany, and the Netherlands; data cut-off date 23^rd^ September 2019): at least two consecutive EORTC QLQ-C30 questionnaires filled in after at least 6 months of follow-up were available for 117 patients; among them, a clinically meaningful deterioration of QoL (reduction of at least 10 points) was observed in 22 (19%) cases during post-curative treatment follow-up.

The second historical cohort comprised 65 patients from Mainz (Germany) having EORTC QLQ-C30 questionnaires completed 24 and 36 months after curative surgery (32). In this population, the percentage of subjects experiencing a deterioration ≥ 10 points in EORTC QLQ-C30 global health status from the 24^th^ to the 36^th^ months after treatments was 23%.

In the Head and Neck 5000 project (UK) (33) repeated global health scores at 12 and 36 months after treatment were available for 1241 people with HNC. A clinically meaningful deterioration of QoL (reduction of at least 10 points) was observed in 18% of these subjects.

In these three existing studies, the average percentage (arithmetic mean) of HNC patients experiencing a clinically meaningful deterioration of EORTC QLQ-C30 global score (reduction of at least 10 points) during follow-up was 20% (19% BD2Decide, 23% Mainz, 18% HN5000). These findings are preliminary and will be explored further as part of the European Union (EU) program supporting this study.

The primary endpoint of this study is the proportion of patients showing a reduction of at least 10 points in EORTC QLQ-C30 global health status score in HNC survivors. Therefore, considering the null hypothesis (*H_0_
*) of no difference for the primary endpoint, the proportion of HNC survivors showing a reduction of at least 10 points in EORTC QLQ-C30 global health status during 24-month FU in the control group is 20% (*µ_0_
*), as derived from the historical benchmark data.

Considering the alternative hypothesis (*H_1_
*), the desired proportion of HNC survivors showing a reduction of at least 10 points in EORTC QLQ-C30 global health status during FU in the intervention group is 10% (*µ_1_

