#### Evaluable cases for primary endpoint

2.5.2

For the purposes of analysis, the study populations are defined in **Table 3**.

**Table 3 T3:** Populations for analysis.

Population	Description
All screened	All participants who sign the informed consent form.
Intent-to-treat (ITT)	All randomized participants whether or not the randomized intervention was administered. This population will be based on the study intervention to which the participant was randomized and will be the primary population for the analysis of efficacy data.
Per-protocol	All randomized participants completing at least two QoL questionnaires 6 months apart, as long as the study participant is disease-free. Participants will be analyzed according to the intervention they actually received.

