#### Questionnaires (both intervention and control arms)

2.5.3

For the primary endpoint, a randomized patient will be considered evaluable given that at least two QoL questionnaires have been completed with the following timing: timing between 2 questionnaires ≥ 6 months as long as the study participant is disease-free.

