#### Study interruption and withdrawal

2.6.7

Participation in the study will be interrupted in case of any of the following conditions apply: death; disease recurrence; diagnosis of second primary malignancy; referred to another center; unable to perform follow-up visits (e.g., due to comorbidities); the participant asked to exit the trial, but allowed the research team to keep patients’ data that they already have collected to be used for research analysis; the participant withdrew his/her consent to the whole study, and wants his/her data to be deleted forever for any future analysis; the participant withdrew his/her consent to the whole study, and wants his/her data to not be used for any future analysis.

Moreover, the participant will discontinue the study when a decrease ≥10 points of global health-related EORTC QLQ-C30 QoL [clinically meaningful deterioration, as defined in (13, 14)] is detected between two questionnaires completed 6 months apart. This will be considered an event for the primary endpoint.

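### The primary-endpoint event is defined inconsistently: on the strict wording, a fall of at least 10 points seen across a missed questionnaire is not captured, although the same patient is evaluable and looser wording would count it

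*Protocol article*

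**What the plan says.** Questionnaires are scheduled at months 0, 6, 12, 18 and 24. Two places tie the event to adjacent visits. Section 2.2, directly after listing these time-points, says that the EORTC scores "will be compared to the respective scores of the previous study time-point". Section 2.6.7 ends participation when a fall of at least 10 points "is detected between two questionnaires completed 6 months apart. This will be considered an event for the primary endpoint".

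Other places are wider. For evaluability on the primary endpoint, section 2.5.3 asks for two questionnaires with "timing between 2 questionnaires ≥ 6 months as long as the study participant is disease-free". The primary objective in Table 1 speaks of a "clinically meaningful deterioration of QoL between at least 2 visits during post-treatment follow-up". The Abstract gives the endpoint as a "decrease ≥10 points) at any point during 24 months post-treatment follow-up". The interruption rule in section 2.2 applies when the deterioration "is detected during the study period, the subject participation in the study will be interrupted", with no interval given.

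Table 3 adds another variant. The per-protocol set is "All randomized participants completing at least two QoL questionnaires 6 months apart", without the word that would admit longer gaps.

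No section says which score is the reference when the previous scheduled questionnaire is missing.

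**The concern.** Three invented patients show the conflict.

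- Patient 1 scores 83 at month 0, misses month 6, and scores 50 at months 12, 18 and 24.
- Patient 2 has only months 0 and 12, scoring 83 and then 50.
- Patient 3 scores 83 at month 0 and 50 at month 6.

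All three are evaluable under 2.5.3, and all three have an observed fall of 33 points. On the strict wording only Patient 3 is an event. Patient 1's month-12 score has no month-6 score to be compared with, and his later steps are zero. Patient 2 has no adjacent pair at all. On the wording of the Abstract and Table 1, all three are events.

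If the strict version were programmed and Patients 1 and 2 stayed in the denominator, each skipped questionnaire would remove up to two comparisons. Event rates would fall in both arms and power would be lost. If the arms skipped at different rates, which is possible in an open-label trial, the arm that skipped more would look better.

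**Working it through.** **The plan's own figure.** Inputs from section 2.5.1: 20% against 10%, one-sided 5% test, 2:1 allocation, 112 control and 224 intervention patients. I used a two-proportion z-test with pooled null variance.

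- Pooled rate = (112 × 0.20 + 224 × 0.10)/336 = 0.1333
- Null SE = √[0.1333 × 0.8667 × (1/112 + 1/224)] = 0.0393
- Alternative SE = √(0.20 × 0.80/112 + 0.10 × 0.90/224) = 0.0428
- Power = Φ[(0.10 − 1.645 × 0.0393)/0.0428] = Φ(0.825) = 79.5%

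Solving for 80% power gives 114/228, close to the stated 112/224. The drop-out step is exact: 112/0.8 = 140 and 224/0.8 = 280. The sample size is not in dispute.

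**Assumptions for the illustration.** The protocol gives no rate of missed single questionnaires, so I used 5% to 30% per visit. Month 0 is always completed. Each later questionnaire is missed independently with probability p, and q = 1 − p. A patient who deteriorates has one lasting fall, equally likely in each of the four intervals. A fall that is not captured is counted as no event.

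**Share of true falls captured.**

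- Adjacent visits only: the first interval needs month 6 (probability q), and each later interval needs both of its ends (q²). The share is (q + 3q²)/4. At p = 10% it is (0.9 + 3 × 0.81)/4 = 0.8325. At p = 20% it is (0.8 + 3 × 0.64)/4 = 0.680.
- Last completed questionnaire: a lasting fall is found if any later questionnaire is completed. The share is [(1 − p⁴) + (1 − p³) + (1 − p²) + (1 − p)]/4. At 10% it is 0.972 and at 20% it is 0.938.

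**Power at 112/224**, with 20% and 10% both multiplied by the captured share:

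| Missed per visit | Adjacent: captured | Adjacent: observed rates | Adjacent: power | Last completed: captured | Last completed: power |
|---|---|---|---|---|---|
| 5% | 91% | 18.3% / 9.1% | 76% | 99% | 79% |
| 10% | 83% | 16.7% / 8.3% | 72% | 97% | 78% |
| 20% | 68% | 13.6% / 6.8% | 64% | 94% | 77% |
| 30% | 54% | 10.8% / 5.4% | 56% | 89% | 75% |

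**No true effect, unequal skipping.** The true rate is 20% in both arms.

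- Control misses 10% and intervention 20%: the observed rates are 16.65% and 13.6%. The one-sided test rejects with probability Φ[(0.0305 − 1.645 × 0.0409)/0.0420] = Φ(−0.875) = 19%.
- Arms reversed: Φ[(−0.0305 − 1.645 × 0.0420)/0.0408] = Φ(−2.44) = 0.7%.
- With the last completed questionnaire as reference, the two figures are about 7% and 4%.

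**A milder model.** The single lasting fall is the harsher case. A simulation with fluctuating scores (an autoregressive state plus error, three assumed variance settings) lost 8–11% of detectable events at 10% missed visits and 16–22% at 20%. The formula above gives losses of 17% and 32%.

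**The benchmarks behind the 20%.** Section 2.5.1 averages three sources, and they do not share one rule. In Head and Neck 5000, "repeated global health scores at 12 and 36 months after treatment were available for 1241 people with HNC", a 24-month gap. The Mainz cohort spans 12 months (months 24 to 36). BD2Decide used at least two consecutive questionnaires. So two of the three count falls over gaps longer than six months, and the third is closer to the adjacent-visit rule.

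**The case against.** The strongest reply is that the plan never says a fall across a gap is ignored. A reader might infer from 2.2 and 2.6.7 that such patients are scored as non-events, but the documents do not support that reading. The Abstract, Table 1 and the interruption rule in 2.2 would all count the fall. Section 2.6.7 says that a six-month fall is an event, not that only such a fall is one. The previous time-point in 2.2 could mean the previous completed one, and the wider interval in 2.5.3 favours that. Section 2.5.6 treats missing data as lack of data and leaves the method open. This stands, and it limits the point to an inconsistency.

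It does not remove the inconsistency. In the examples both scores are observed, so a missing-data method does not decide whether the fall is an event. Nor can the matter simply wait for the comprehensive statistical plan. Section 2.5.6 schedules that plan after data collection, while 2.6.7 uses the event definition to end participation during the trial.

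The objections to the size also stand in part.

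- Section 2.6.5 provides telephone contact and remote completion, which should reduce skipping.
- The roughly 30% non-return at six months in the eHealth trial cited in the Introduction is described there as drop-out, so it is not a per-visit skipping rate.
- The 112/224 already allows for 20% drop-out, so including permanent loss in p would partly count it twice.
- Nothing in the protocol indicates which arm would skip more.

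**Conclusion.** The concern holds as an inconsistency in the definition of the primary event. On the strict wording of 2.2 and 2.6.7, an evaluable patient can have an observed fall of at least 10 points that no rule captures. On the wording of the Abstract and Table 1 the same fall counts. It should be settled because it affects the primary endpoint and its secondary time-to-event version, and because sites act on the definition during follow-up.

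The size is conditional. If the strict wording is applied and these patients stay in the denominator, 10% to 20% missed visits would bring power from 79.5% to between 72% and 64%. Under no effect, rejection would be about 19% or about 0.7%, depending on which arm skips 20% rather than 10%. These figures rest on assumed independent skipping and a single lasting fall. They illustrate what the wording could cost and do not predict this trial's result.

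**What to change.** For the primary-endpoint analysis, state in section 2.2 that each global score is compared with the most recent completed earlier questionnaire, whatever the gap. Events and evaluability (2.5.3) then use the same pairs. For time to first deterioration, treat a fall across a missed visit as interval-censored between the two completed questionnaires. Keep the adjacent-visit version as a sensitivity analysis.

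The interruption wording in 2.2 and 2.6.7 and the per-protocol wording in Table 3 must be reconciled with that definition. When participation should stop is for the trial team to decide, and this review does not propose a rule.

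The cost is a few sentences and a small change to the derivation program. The downside is that patients who skip a visit are compared over a longer interval, so comparison intervals become slightly less uniform.

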### Study population

2.3

Each participating Center (recruiting patients in Italy and the United Kingdom) will enroll consecutive patients according to the eligibility criteria listed below.

#### Inclusion criteria

2.3.1

Effectively cured histologically defined head and neck squamous cell carcinoma (HNSCC) from one of these subsites: oral cavity, nasopharynx, hypopharynx, larynx, Human Papillomavirus (HPV)-positive or negative oropharynx, nasal cavity, paranasal sinuses. Non-metastatic salivary gland cancer (SGC) of any histological type can be included only if curative or postoperative radiotherapy included the neck:For p16-negative or p16-unknown HNSCC (including nasal cavity and paranasal sinuses), stage I, II, III, IVa or IVb (no IVc) according to UICC/AJCC 8^th^ edition. Regional neck metastases from squamous cell carcinoma from unknown primary head and neck sites are allowed.For nasopharyngeal cancer (NPC), stage I, II, III, IVa (no IVb) according to UICC/AJCC 8^th^ edition. Regional neck metastases from EBV-positive carcinoma from unknown primary head and neck sites are allowed.For SGCs, stage III, IVa or IVb according to UICC/AJCC 8^th^ edition treated with radiotherapy that included the neck (either post-operative radiation or radical treatment in case of unresectable disease).For p16-positive oropharyngeal squamous cell carcinoma, stage I, II or III according to UICC/AJCC 8^th^ edition. Regional neck metastases from p16-positive and/or HPV-positive squamous cell carcinoma from unknown primary head and neck sites are allowed.Patients having completed treatment with curative intent (including any single modality or multimodal approach) within 10 years at the time of accrual.Patients being disease-free at the time of accrual. Patients will be deemed in complete remission if the clinical examination is negative for recurrence; clinical examination should be preferably, but not mandatorily, integrated with unequivocal radiological imaging that shows the absence of disease (in case of doubt, further radiological imaging should be performed or integrated with cyto/histological samples of the area with suspected disease persistence and the exams will have to be consistently negative) after at least three months following treatment completion.Ability to fill in questionnaires as per protocol.Geographical accessibility and willingness to be followed-up for up to 2 years with information-technology (IT) devices in addition to questionnaires.Age ≥ 18 years.Signed informed consent.Willingness to use their smartphone and their Internet access for the study.Smartphone having the following minimum characteristics:RAM: Minimum of 2 GBStorage: Minimum of 512 MB free storageOperating system: Android version 7 (Nougat) or upper.
